### Blinding

It is not possible to blind the observer because the implant migration is assessed using radiostereometric analysis. However, patient-reported outcomes are solely assessed by the patients before the follow-up examination, without involving the surgeon or observer. The patients will be blinded to their allocated treatment the first 2 years after surgery.

The statistician, who performs the analysis, is blinded to the randomization.

### Surgical procedure

The procedures will be performed at Herlev and Gentofte Hospital, Copenhagen University Hospital. This unit performs around 300 primary and revision shoulder arthroplasties each year. From the evaluation of the number of surgeries from 2015 to 2016, it is expected to perform surgery on 75 patients with reverse shoulder arthroplasty for rotator cuff arthropathy every year. To minimize a potential learning curve and ensure a high surgical standard, the study is performed as a single-centre study and six experienced shoulder surgeons will be performing this type of surgery regularly using the same implant. To determine the potential learning curve applied by the lateralization devices, there will be done subgroup analyses at the end of the study, to compare the first and second half of the patients. Prior to the initiation of the study, each of the six surgeons shall have performed a minimum of 3 surgeries with the DELTA Xtend Reverse Shoulder System Lateralized Glenosphere Line Extension to minimize a potential learning curve problem.

The patient is under general anaesthesia and in a beach chair position during the procedure. Surgical technique, including soft tissue balancing and exposure instrumentation, is standardized for all patients. All surgeries are done with the standard deltopectoral approach and subscapularis tenodesis. All patients are treated with either (1) DELTA Xtend Reverse Shoulder System Lateralized Glenosphere Line Extension or (2) the standard DELTA Xtend Reverse Shoulder System according to the guidelines from the manufacturer. Perioperatively, approximately 20 tantalum markers (0.8 mm, Tilly Medical Products, Lund, Sweden) are placed in the bone at the proximal humerus and the glenoid around the components; we aim for the widest non-linear distribution, which will allow us to measure segmental motion with Mb-RSA software (Model-based RSA 4.1, 2003-2014 RSAcore Department of orthopedics Leiden University Medical Centre) using computer-aided design (CAD) models.

Size 1 and 2 humeral components will be used, in which all patients are treated with a cemented humeral monobloc component. Based on the medialization measured by plain radiographs, there will be used a 4-mm or 8-mm lateralized glenosphere if randomized for the intervention group. If randomized for the control group, a standard glenosphere is used. Prophylactic cloxacillin 2 g and benzylpenicillin 1.2 g are given preoperatively and at 6 and 12 h. If a patient cannot tolerate the standard prophylactic treatment, cefuroxime 1.5 g is given preoperative and at 6 and 12 h.

### Rehabilitation

All patients will receive a standard rehabilitation program led by a physiotherapist. A physiotherapist will one day postoperative instruct the patients in oedema prophylaxis. The patient will use a sling for 2 weeks, after which the patient has an appointment with the physiotherapist at the hospital for instructions in non-weight bearing training. Subsequently, the patient has an appointment with the physiotherapist once a week. There is a minimum of 3 months of training, longer if needed. Weight-bearing training is allowed after 6 weeks.

### Outcome measures

#### Primary radiological outcome

Migration of the glenoid components is assessed by model-based radiostereometric analysis, which is performed according to the guidelines of Valstar and Colleagues [12]. In this part of the study, the first 56 patients are included. Maximum total point motion (MTPM) after 2 years of follow-up is compared to the baseline value and is used as the primary radiostereometric analysis effect parameter. The accuracy of radiostereometric analysis will be assessed by at least 12 double examinations. The reference examination will be done within 1 week after the surgery, and the follow-up examinations are planned at 3 months, 6 months, 1 year and 2 years. Radiostereometric analysis is conducted using a uniplanar radiostereometric analysis arrangement (UmRSA®- Calibration Cage No 43 (hip, spine and shoulder)). The x-ray analysis is performed using the model-based radiostereometric analysis commercial software (RSAcore, Department of Orthopedics, Leiden University Medical Center, Leiden, The Netherlands), available at the Skaane University Hospital, Lund Sweden, where the analyses of radiostereometric analysis-x-rays will be conducted. The exact set-up for the radiostereometric analysis (e.g. various distances and the degree between the 2 x-ray tubes) will be specified from a small phantom study and measurements of the 6 pilot patients (3 with each of the 2 types of implants). 42 combined CAD models for MB-RSA will be delivered by Depuy Synthes (Raynham, MA, USA).

#### Primary functional outcome

*WOOS score*: The WOOS score is a disease-specific patient-reported outcome [18]. It contains 19 questions, divided into four groups: sports and work, physical symptoms, emotions, and lifestyle. The questions are answered using a visual analogue scale ranging from 0 to 100. The overall score is from 0 to 1900, where 1900 is the worst result. The scores are converted into a percentage of the maximum score to ease the interpretation. The difference in mean score between the preoperative score and the 2-year follow-up score is the primary value of interest. In this study, there is used a version of WOOS, which has been translated to Danish according to the guidelines of Guillemin, Bombardier and Beaton [19]. This version has been validated with classical test theory in a cohort of patients treated with shoulder arthroplasty for osteoarthritis [21].

#### Secondary radiological outcomes

*Plain radiographs*: the plain radiographs will be taken preoperatively, in the first week postoperatively, at 3 months, 1 year and 2 years. There will be used an anterior-posterior and lateral view. The radiographs will be used for evaluation of inferior scapular notching.

*DXA*: the first 56 patients will be included in this part of the study. DXA will be conducted preoperatively to evaluate BMD of the proximal humerus, scapula and distal forearm. BMD measurements of the distal forearm will be performed bilateral and used as reference to the shoulder and to adjust for changes in BMD that are not related to the shoulder arthroplasty. The difference in mean score between the preoperative BMD score and the 2-year follow-up score is the primary value of interest as it represents the change after the implant. The precision of DXA will be assessed by 12 double examinations.

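### The preoperative-to-2-year BMD difference spans the operation itself, so within an arm it cannot be read as change after implantation

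*Protocol article*

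**What the plan says.** The DXA paragraph under Secondary radiological outcomes sets the baseline and the regions: "DXA will be conducted preoperatively to evaluate BMD of the proximal humerus, scapula and distal forearm". It then fixes the outcome: "The difference in mean score between the preoperative BMD score and the 2-year follow-up score is the primary value of interest", and gives the reason: "as it represents the change after the implant". Both distal forearms are scanned and are "used as reference to the shoulder and to adjust for changes in BMD that are not related to the shoulder arthroplasty".

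The Surgical procedure section describes what happens to the shoulder between the two scans. At the humerus, "all patients are treated with a cemented humeral monobloc component". About 20 tantalum markers "are placed in the bone at the proximal humerus and the glenoid around the components". The glenosphere depends on allocation: "there will be used a 4-mm or 8-mm lateralized glenosphere if randomized for the intervention group", against a standard glenosphere in the control group.

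For RSA, in the same first 56 patients, Primary radiological outcome uses a postoperative starting point: "The reference examination will be done within 1 week after the surgery".

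The Statistics section expects to analyse pre- to postoperative changes with paired parametric tests, group differences with parametric tests, and the overall results with a mixed effects model.

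**The concern.** The article does more than name a baseline. It attaches a meaning to the resulting difference, and that meaning does not follow. The first scan shows the native shoulder. The second shows the same regions with cement, metal and markers in or next to the bone. A rise or fall between them may reflect what was put in at surgery, what the bone did over the next two years, or both.

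At stake is the reading of the within-arm result. The Statistics section expects paired pre- to postoperative tests, so a within-arm BMD change is likely to be reported with a p-value. Under the stated justification it would be read as bone gain or loss around the implant.

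**Working it through.** No BMD mean, SD or target difference is given, so the check is algebraic.

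**1. Notation, for one shoulder region in one patient.**
- B0: BMD on the preoperative scan
- B1: BMD on a scan within 1 week after surgery (hypothetical for DXA, since the DXA paragraph does not mention one)
- B2: BMD at 2 years
- S = B1 − B0: the immediate operative step
- R = B2 − B1: the change after implantation

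**2. What the planned outcome measures.**
B2 − B0 = (B1 − B0) + (B2 − B1) = S + R.
The justification treats B2 − B0 as R. That is true only if S = 0. The stem, cement and markers all enter between B0 and B1, so nothing in the article supports S = 0. Bone removal would add to S, but the article does not describe it, and the argument does not need it.

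**3. Whether the forearm reference removes S.**
Let the forearm change over the same interval be G. The forearm has no operative step, so G contains only change unrelated to the arthroplasty. The adjusted shoulder change is (S + R) − G = S + (R − G). The adjustment acts on R and leaves S in full.

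**4. The within-arm mean.**
E(B2 − B0) = E(S) + E(R). A paired test of this mean against zero tests the sum. Read as a test of E(R), it is biased by E(S).

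**5. The between-arm contrast** (L lateralized, C control).
Difference = [E(S | L) − E(S | C)] + [E(R | L) − E(R | C)].
- *Proximal humerus:* the cemented monobloc component and the markers are common to both arms and allocation is random, so the first bracket is expected to be zero. The contrast is unbiased for the difference in later change.
- *Scapula:* the glenosphere differs by arm. The first bracket is non-zero only if the implant affects the measured scapular BMD. That depends on how the region is drawn and how metal is excluded, neither of which is given.

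**6. The only related sample size.**
The first 56 patients come from the RSA calculation: SD 0.4 mm, difference 0.4 mm, power 0.90, significance level 5% (taken as two-sided).
n per group = 2 × (1.960 + 1.282)² × (0.4/0.4)² ≈ 21.01, rounded up to 22. With 20% drop-out, 22/0.80 = 27.5, rounded up to 28 per group, so 56 in total.
This reproduces the stated figure. BMD does not enter it, so changing the DXA reference scan leaves it unchanged.

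**The case against.** **The wording may be loose rather than wrong.** Net change from before surgery to 2 years is a legitimate quantity, and the article uses the same formula for its questionnaire and functional scores. For those scores the effect of the operation is exactly what is wanted. For BMD the measured tissue is itself altered by the implant, so net change and change after implantation are different quantities. The article names the first and claims the second.

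**The RSA parallel is inexact.** This is correct: migration needs an implant in place, so RSA could not have a preoperative reference. The RSA schedule shows only that these patients already attend a visit within a week of surgery.

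**The schedule figure may list a postoperative DXA.** Fig. 3 is not shown, and the planned mixed model suggests repeated measurements. Such a scan would make the fix easier, but the text would still name the preoperative scan as the baseline.

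**Randomisation protects the comparison that matters.** At the humerus this stands in full.

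Some stronger readings are tempting, and the documents do not support them:
- *The scapular comparison is biased by implant geometry.* This requires glenosphere metal to affect the measured region, and the article gives neither region limits nor metal handling. Such detail is commonly left to a full protocol.
- *The between-arm comparison loses a calculable amount of power.* Var(S + R) = Var(S) + Var(R) + 2 Cov(S, R). Precision falls only if Var(S) + 2 Cov(S, R) is positive, and none of these terms is given. Neither the size nor the direction of an effect on power is established.
- *The operative step makes up the greater part of the difference.* No figure in the article bears on the relative sizes of S and R.

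**Conclusion.** The stated justification is wrong. Within an arm, the preoperative-to-2-year difference at the proximal humerus and scapula combines the operative step with later bone change, and the forearm adjustment does not separate them. This rests on the cemented stem, the glenoid component and the markers, all of which the article states. A possible intraoperative conversion to hemiarthroplasty, allowed under Protocol violations, does not change the argument at the humerus.

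The bias in the within-arm reading equals the mean operative step, whose size and sign the documents do not allow one to estimate. The randomised humeral contrast is sound, and an arm-specific scapular shift remains only a possibility. The point concerns one secondary outcome. Neither co-primary outcome nor either sample size is affected. It merits correction because, without an early postoperative scan, change after implantation cannot be recovered at analysis.

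**What to change.** **Preferred.** For the proximal humerus and scapula, define the DXA value of interest as the change from the first postoperative scan, at the within-1-week visit, to 2 years. Keep the preoperative scan as a descriptor or covariate. The Enrolment section uses it to assess native bone density and osteopenia of the proximal humerus, so it should not be given up. Keep the forearm as reference, preferably scanned at the same visits so that the intervals match.

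**If Fig. 3 has no early postoperative DXA and the sponsor does not add one.** Delete the claim that the difference represents change after the implant. Describe it as net change including the operation, and interpret only the between-arm comparison.

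**Cost.** If the early scan is already scheduled, or if the fallback is chosen, this is a wording change. Otherwise it means one additional DXA in up to 56 patients, at a visit they already attend for RSA. The extra radiation dose of 0.10 mSv stated under Enrolment would then need to be rechecked.

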#### Secondary functional outcomes

*Constant-Murley Score*: The Constant-Murley Score includes an evaluation of pain, range of motion, activities of daily living and strength. The maximum score for the evaluation of pain and activities of daily living is 35 points. For the objective evaluation, there is a maximum score of 65 points, of which 40 are from a range of motion and 25 are from strength. Thereby there is a collected maximum of 100 points, which indicates a shoulder without any disabilities. The difference in mean score between the preoperative score and the 2-year follow-up score is the primary value of interest. In this study, a Danish version [22] of the modified Constant score [23] is used.

*Oxford Shoulder Score (OSS)*: The OSS was invented as a measurement tool to assess function and pain after elective shoulder surgery [24]. It contains 12 questions with a score from 0 to 4. The total score ranges from 0 to 48, with 48 as the best score. The scores are converted into a percentage of the maximum score to ease the interpretation. The difference in mean score between the preoperative score and the 2-year follow-up score is the primary value of interest. In this study, the Danish version, which has been translated and validated with the classical test theory [25], of OSS is used.

*Complications and side effects*: Any incident of medical (cardiovascular, embolism, pneumonia) and surgical complications (nerve damage, fracture, infection, instability, disposition of component and dislocation) will be noted, as well as revision surgery (removal or exchange of any component).

*Pain and patient satisfaction*: Pain is evaluated on the day of examination with the VAS score with scores from 0 to 10, with 10 points as the worst possible pain. The patients will describe the outcome on a 7-point scale, with ‘much better’ as the best and ‘much worse’ as the worst. The difference in mean score between the preoperative score and the 2-year follow-up score is the primary value of interest.

*Economic assessment*: Quality-adjusted life years (QALY) is determined from the threshold of the acceptable cost-utility ratios for the health care system to use. In, respectively, Europe and England, the thresholds are set at 30,000 Euros and 20,000–30,000 pounds. The study will compare the cost-utility of the DELTA Xtend Reverse Shoulder System Lateralized Glenosphere Line Extension with the set thresholds and the cost-utility of the Standard DELTA Xtend Reverse Shoulder System. To estimate the QALY for each patient, there will be used EQ-5D-5 L. The difference in mean score between the preoperative score and the 2-year follow-up score is the primary value of interest. There will be defined a cost model from medical records, registries, data from patients and unit costs from the Danish health care system. Information regarding usage and readmission of pain medication, length of hospital stay and discharge destination will be noted.

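### The economic assessment derives QALYs from the threshold, centres on a two-point EQ-5D change, and compares cost-utility ratios that are not the incremental cost per QALY

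*Protocol article*

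**What the plan says.** The economic assessment is one paragraph under Secondary functional outcomes in the protocol article. It makes these statements, in this order:

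- On the QALY itself: "Quality-adjusted life years (QALY) is determined from the threshold of the acceptable cost-utility ratios for the health care system to use".
- On the thresholds, for Europe and England respectively: "the thresholds are set at 30,000 Euros and 20,000–30,000 pounds".
- On the comparison: "The study will compare the cost-utility of the DELTA Xtend Reverse Shoulder System Lateralized Glenosphere Line Extension with the set thresholds". The same sentence adds a second comparator: "with the set thresholds and the cost-utility of the Standard DELTA Xtend Reverse Shoulder System".
- On measurement and the summary measure, in two consecutive sentences: "To estimate the QALY for each patient, there will be used EQ-5D-5 L. The difference in mean score between the preoperative score and". Its other end is the score at 2 years, and this change is named as the main quantity for the outcome.
- On costs: "There will be defined a cost model from medical records, registries, data from patients and unit costs from the Danish health care system".

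No incremental ratio is named.

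**The concern.** Three statements are wrong or badly fixed.

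1. **The QALY and the threshold are confused.** A threshold is what a payer will give for one QALY. It is a price, and it cannot determine how many QALYs a patient has had.
2. **The summary measure has no time dimension.** A QALY is utility multiplied by the time spent at that utility. A difference between a preoperative and a 2-year score ignores how quickly patients recover. It also ignores any temporary loss from a complication or revision that has resolved by 2 years.
3. **Neither planned comparison is the one the thresholds are for.** The thresholds apply to the extra cost per extra QALY of one option over its alternative. The plan sets the lateralized system's own cost-utility against them and, separately, against the cost-utility of the standard system. The trial has two active arms and no unoperated arm, so an implant's own ratio would also rest on before-after change and not on the randomized contrast.

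Economy is a named secondary outcome. The Background argues that a small number of additional revisions could make the lateralized component economically unattractive. The Discussion expects the implant to be taken up without further testing if an advantage is shown. An economic result that can point the wrong way would feed into that decision.

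**Working it through.** The article states no QALY, cost or ratio, so there is no figure to reproduce. All utilities and costs below are assumed, to show what the stated rules can do. Only the thresholds and the visit times (preoperative, 3, 6, 12 and 24 months) come from the article.

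**Step 1. Two-point change against accumulated utility**

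Formula: QALY = sum over intervals of (mean of the two end utilities) × (interval length in years). Every path below starts at 0.50 and ends at 0.80, so the change score is always 0.30.

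Moderately different recovery, times 0, 0.25, 0.5, 1 and 2 years:
- Faster path 0.50, 0.75, 0.80, 0.80, 0.80: 0.15625 + 0.19375 + 0.400 + 0.800 = 1.550
- Slower path 0.50, 0.60, 0.65, 0.70, 0.80: 0.1375 + 0.15625 + 0.3375 + 0.750 = 1.381
- Difference: 0.169 QALY

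Extreme contrast:
- Full gain by 3 months: 0.25 × (0.50 + 0.80)/2 + 1.75 × 0.80 = 1.5625
- Linear gain over 24 months: 2 × (0.50 + 0.80)/2 = 1.30
- Difference: 0.2625 QALY, or 0.2625 × 30,000 = 7,875 euros at the European threshold

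If both arms follow the same path, the difference is 0. The change score reports no difference in all three cases.

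**Step 2. Own ratio against incremental ratio**

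Assumed: cost 10,000 euros (standard) and 12,000 euros (lateralized); 0.45 QALY gained on the standard system relative to staying at the preoperative utility; d extra QALYs on the lateralized system.

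- Standard system's own ratio: 10,000 / 0.45 = 22,222
- Lateralized system's own ratio: 12,000 / (0.45 + d)
- Incremental ratio: (12,000 − 10,000) / d

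| d | Lateralized, own ratio | Incremental ratio | Incremental ratio against 30,000 |
|---|---|---|---|
| 0.02 | 25,532 | 100,000 | above |
| 0.05 | 24,000 | 40,000 | above |
| 0.08 | 22,642 | 25,000 | below |
| 0.10 | 21,818 | 20,000 | below |
| 0.20 | 18,462 | 10,000 | below |

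Two results follow.

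- **Against the threshold.** The lateralized system's own ratio is below 30,000 in every row. It would be below even with no extra benefit at all: 12,000 / 0.45 = 26,667. At d = 0.02 and 0.05 it passes although the incremental ratio does not.
- **Against the standard system's ratio.** At d = 0.08 the lateralized system looks worse (22,642 against 22,222), although each extra QALY costs 25,000, below the threshold.

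So each planned comparison can give the wrong answer, and in this example they err in opposite directions.

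**The case against.** The strongest reply is that the paragraph is loosely worded and condensed, and that a sound analysis may lie behind it. Several parts of that reply stand.

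- **Change score as QALY.** A reader might infer that the plan defines the QALY as the EQ-5D change. The text does not say so. It gives no formula, and the change-score sentence also appears for WOOS, Constant-Murley, OSS and pain, so it may simply have been carried over. What remains is that this sentence fixes the main quantity of the economic outcome, directly after the sentence on the QALY.
- **No comparison between implants.** A reader might infer that each implant is merely held against the threshold. In fact only the lateralized system is, and a comparison with the standard system is planned. That comparison could be carried out incrementally. As worded, it sets one cost-utility against another, which Step 2 shows is a different thing.
- **Missing detail.** Value set, baseline adjustment and interval methods are commonly left to a fuller document, and the EQ-5D-5L schedule is in figures not shown. None of that is held against the plan. The visits listed under Follow-up would allow a time-based QALY.
- **Costs are captured.** The cost model, together with the recording of complications and revisions, would pick up the cost of these events. It would not pick up the utility lost meanwhile.
- **Illustrations are assumed.** The 0.26 QALY contrast is extreme, and both arms receive the same rehabilitation. It is not an expected error for this trial.

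The reply does not rescue the sentence that derives the QALY from the threshold. No fuller document would make that correct.

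**Conclusion.** The point holds in limited form: the economic paragraph is wrong as written in three statements. It derives the QALY from a price, it makes a two-point change the main quantity for an outcome that needs utility over time, and it plans comparisons that are not the incremental cost per QALY gained.

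The size cannot be estimated from the article. Under the assumed values, a change-score comparison hides 0 to 0.26 QALY, with 0.17 for moderately different recovery. An own ratio of 24,000 can accompany an incremental ratio of 40,000. The actual error depends on how far recovery paths, costs and utilities differ between arms. If the arms recover along the same path, the change score hides nothing, though the problem with the ratios remains.

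It would go too far to say that the planned comparison is meaningless; it can mislead. The point concerns one secondary outcome and does not touch the co-primary outcomes or the sample size.

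**What to change.** Reword the economic assessment as follows.

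1. Delete the sentence that derives the QALY from the threshold. Keep the thresholds as decision values only.
2. Define each patient's QALY as the area under the EQ-5D-5L utility curve over 2 years, using every visit at which the questionnaire is collected. The preoperative-to-2-year change may still be reported, as a description of the EQ-5D score.
3. Estimate the between-arm difference in QALYs, adjusted for preoperative utility.
4. Compare the incremental cost per QALY gained, lateralized versus standard, with the stated thresholds, or report net monetary benefit at those thresholds.

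The cost is a change of wording and slightly more analysis work. EQ-5D-5L is already completed preoperatively, and follow-up visits exist at 3, 6, 12 and 24 months. If the schedule figures show that the questionnaire is not given at an intermediate visit, one short form would be added there.
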